### Sample size

Sample size calculation was informed by data of a cohort study with the same population [32]. Data gave evidence of an ICC = 0.04 and an expected standard deviation of 25. A cluster size of 10 is assumed, i.e. the variance inflation factor is 1 + (10 − 1) × 0.04 = 1.36. The study plans to detect a score difference between intervention groups of at least 12 points [30] on a two-sided alpha level of 0.05 with a power of 80%, resulting in a total sample size of ((1.96 + 0.84)^2^ × 2 × 25^2^ × 1.36)/12^2^ = 92.6. Recruitment of 12 clusters à 10 patients accounts for a dropout rate of 23%. The study will be conducted in two waves, resulting in six clusters (three per study centre) à ten patients being recruited per wave. Current experience shows that a few clusters will possibly fail to recruit the necessary number of patients. In this case, we will recruit more patients in other clusters to compensate for this. To maintain the statistical power of the study, the following rule will be applied: number of patients to be additionally recruited in other clusters = 1.5 × number of patients that some clusters fail to recruit.

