### Health economic evaluation

The objective of the health economic evaluation is to estimate the cost-effectiveness of the intervention in terms of additional costs per additional patient who experienced a decrease of 12 points on the DHI questionnaire between *t*_0_ and *t*_2_. Moreover, a cost-utility analysis will consider the additional costs per additional quality-adjusted life year (QALY).

The health economic evaluation will be performed from a societal perspective. Therefore medical and non-medical resource utilisation will be measured for retrospective periods of 6 months at baseline and at *t*_2_ using the Health-Related Resource Use in an Elderly Population. For monetary valuation of resource utilisation, unit costs will be calculated for all services and goods (privately purchased or prescribed) in Euro.

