### Data analysis

The data analysis of the measured outcomes will be done by a blinded biostatistician who is not involved in the study. The primary analysis will be based on a linear mixed model of the DHI changes between t_0_ and t_2_, using intervention group and initial DHI as fixed factors and a random intercept for cluster. The statistical inference will be based on the Wald *t*-test for the intervention on an alpha level of 5% (two-sided). Similar models will be applied for exploratory analyses of the secondary outcomes. No pre-specified subgroup analyses are planned. Due to the restricted sample size, no additional adjustments for other fixed effects are planned. Range and cross-checks of the outcome variables and key baseline patient characteristics will be performed. Impossible or implausible data will trigger queries to the team of the principal investigator. All analyses will be based on the intention-to-treat principle. In case of dropouts, the last available observation will be carried forward. No interim analyses are planned.

For the process evaluation, quantitative data will be analysed descriptively. Qualitative data from interviews and field notes from research team, GPs and PTs will be analysed with content analysis [50], which will be performed by two independent researchers from the study centres.

To analyse the cost-effectiveness of the intervention, an incremental cost-effectiveness ratio and an incremental cost-utility ratio will be calculated as the ratio of the difference in mean cost and the difference in mean health effects (DHI or QALY) between study groups during the 6-month follow-up period. Non-parametric bootstrap method will be employed to generate confidence intervals around the difference in mean cost and the difference in mean health effects. Uncertainty surrounding the cost-effectiveness ratio and cost-utility ratio will be presented on the cost-effectiveness plane. Furthermore, cost-effectiveness acceptability curves, based on the incremental net-monetary benefit will be constructed. The study will be terminated when all collected data have been analysed and utilised within the analysis plan.

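### The cost-effectiveness objective counts patients with a 12-point DHI decrease, but the analysis section divides by the difference in mean DHI; the bootstrap's resampling unit is also not stated

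*Protocol article*

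**What the plan says.** Under Health economic evaluation, the objective is to estimate "additional costs per additional patient who experienced a decrease of 12 points on the DHI questionnaire" from t0 to t2. A separate cost-utility analysis uses QALYs.

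Under Data analysis, the incremental ratios are the difference in mean cost over "the difference in mean health effects (DHI or QALY) between study groups during the 6-month follow-up period". For uncertainty the same paragraph says: "Non-parametric bootstrap method will be employed to generate confidence intervals around the difference in mean cost and the difference in mean health effects". It adds a cost-effectiveness plane and acceptability curves based on incremental net monetary benefit. It does not name the unit that is resampled.

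Three other statements bear on this:

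- The primary model is specified "using intervention group and initial DHI as fixed factors and a random intercept for cluster".
- For the secondary outcomes the plan says: "Similar models will be applied for exploratory analyses of the secondary outcomes".
- On the design inputs, the Sample size section says: "Data gave evidence of an ICC = 0.04 and an expected standard deviation of 25". With a cluster size of 10 it derives an inflation factor of 1.36.

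**The concern.** The objective concerns a proportion: how many more patients reach a 12-point decrease. The analysis names DHI, which the Outcomes section defines as a score from 0 to 100. A ratio on mean DHI is in euros per point; the objective asks for euros per additional responder. A willingness-to-pay value, which the acceptability curves need, has to be expressed per unit of effect, and the two sections give different units. If this stays open, the effect measure can be settled after the data are seen.

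The second issue is how uncertainty is estimated. Practices are randomised, and both the sample size and the primary model allow for that. The economic paragraph sets out its own method and does not mention practices. If the bootstrap drew individual patients regardless of practice, the intervals, the plane and the acceptability curves would show more certainty than the design supports.

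**Working it through.** **The plan's own figure.** Inflation factor: 1 + (10 − 1) × 0.04 = 1.36. This reproduces. The article gives no numerical figure for the economic analysis itself.

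**Effect measure.** The check is whether a mean difference in DHI fixes the responder difference.

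- Inputs: a 12-point mean difference (Sample size) and a response threshold of a 12-point decrease (Health economic evaluation).
- Assumptions, not in the article: normally distributed changes with the same SD in both arms, SD of change 15 to 25, control mean change 0 to −12.
- Formula: P(response) = Φ((−12 − mean change) / SD). The intervention mean is the control mean minus 12.

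| SD | Control mean | Control responders | Intervention responders | Difference |
|---|---|---|---|---|
| 25 | 0 | 0.316 | 0.500 | 0.184 |
| 25 | −6 | 0.405 | 0.595 | 0.190 |
| 20 | −12 | 0.500 | 0.726 | 0.226 |
| 15 | 0 | 0.212 | 0.500 | 0.288 |
| 15 | −6 | 0.345 | 0.655 | 0.311 |

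The same 12-point mean difference therefore gives 18 to 31 percentage points more responders. For a fixed cost difference, cost per responder is cost per point times 12 / (responder difference). That factor runs from 12 / 0.311 ≈ 39 to 12 / 0.184 ≈ 65, so one ratio cannot be read off the other.

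**Resampling unit (conditional).** Suppose patients were drawn without regard to practice.

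- Design effect: D = 1 + 9 × ICC.
- Width relative to the correct interval: 1/√D.
- Coverage of a nominal 95% interval: 2Φ(1.96/√D) − 1.

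| ICC | D | Relative width | Coverage |
|---|---|---|---|
| 0.01 | 1.09 | 0.96 | 94.0% |
| 0.04 | 1.36 | 0.86 | 90.7% |
| 0.10 | 1.90 | 0.73 | 84.5% |

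The ICC of 0.04 is the article's value for its sample size on DHI. None is given for costs or QALYs, so 0.01 and 0.10 are an assumed range. A simulation of 2,000 trials (six practices of 10 per arm, 600 resamples each) gave patient-level coverage of 93.1%, 90.4% and 82.9%.

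**Would resampling whole practices be enough?** In the same simulation a plain percentile bootstrap of practices covered 88.7% to 89.3% across these ICCs. This is expected with six practices per arm. The bootstrap variance is too small by a factor of 5/6, and the normal quantile stands in for a t quantile on 10 degrees of freedom. The effective multiplier is 1.96 × √(5/6) = 1.79, and P(|t| < 1.79) on 10 degrees of freedom is about 90%.

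**The case against.** On the effect measure, the best defence is that the parenthesis naming DHI and QALY is shorthand for the two analyses already defined under Health economic evaluation. The mean of a 0/1 responder indicator is a proportion, so a difference in mean effects could be the responder difference. That reading is possible but is not written: the Data analysis section names DHI, and elsewhere DHI means the score. The defence lowers the seriousness of the conflict without removing it. Because two printed statements differ, this is not a detail left to a fuller plan.

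On the bootstrap, a reader might infer that the plan ignores clustering and that its intervals are therefore too narrow. The article does not support that. A bootstrap that resamples practices is also non-parametric, and the resampling unit is something an article may leave to an analysis plan that is not shown here. At an ICC of 0.01 the loss of coverage would in any case be small.

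A reader might also infer that baseline utility and cost are collected and then not used. This is not shown either. The article says "resource utilisation will be measured for retrospective periods of 6 months at baseline and at" t2, and EQ-5D-5L and resource use are both listed among the secondary outcomes, for which models similar to the primary one are promised. Whether baseline values also enter the economic comparison is not stated. Leaving them out would not narrow the intervals; it would usually widen them or leave chance imbalance in the estimate.

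**Conclusion.** The mismatch in effect measure stands, on the text alone. As written, the planned ratio is a cost per DHI point and does not answer the stated objective. The 18 to 31 percentage points illustrate why the two are not interchangeable; they rest on the assumed normal changes, SDs and control means. Which reading was intended cannot be told from the article.

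The clustering point stands only as a condition: if patients are resampled without regard to practice, coverage falls to about 91% at the ICC used for DHI, with a range of about 94% to 84.5% for ICCs of 0.01 to 0.10. It is a reason to state the resampling unit and is not evidence of an error.

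The primary outcome and its test are unaffected. The matter should be settled before the economic analysis is run, because the headline economic ratio currently has two definitions.

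**What to change.** 1. In Data analysis, define the cost-effectiveness effect as the between-group difference in the proportion of patients with a DHI decrease of at least 12 points from t0 to t2, to match the objective. Keep QALYs for the cost-utility ratio. A ratio on mean DHI may stay as an additional analysis, labelled as such.
2. State how the economic intervals, the plane and the acceptability curves respect practices. Keep each patient's cost and effect together, and use a method suited to six practices per arm. Examples are a two-stage bootstrap with shrinkage correction, or a joint mixed model for cost and effect with small-sample degrees of freedom. A plain bootstrap of practices is not enough, since it covers only about 89%.

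The cost is a few sentences and some programming, with no change to data collection or trial conduct. The price is wider intervals than patient-level resampling would give: at an ICC of 0.04 the correct width is √1.36 = 1.17 times as large, and a small-sample correction adds to that.

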### Harms

In order to monitor the unintended consequences of the study, we will stay in contact with the GPs, and PTs have implemented a telephone hotline for all participant groups, review the notes on the checklists, decision trees and physical activity diary and conduct interviews with patients.

Additionally, an advisory board, consisting of members of the MobilE-Net Network, will supervise the trial.

## Discussion

Due to the experiences gained from our pilot study, we have critically and carefully revised our recruitment, intervention and implementation strategies. First, the recruitment options are expanded in terms of the use of various approaches (e.g. involvement of local networks, use of faxes, call for participation via website and newspaper). Medical assistants are incorporated in the whole study process, as they are the primary point of contact with the practice and relationships with practice staff are considered as essential for maintaining commitment to the study [51, 52]. The adherence to the intervention protocol by the GPs and PTs will be improved by using a revised version of the checklist and decision tree, revised educational trainings (e.g. more hands-on exercises), the provision of supportive materials and a study folder with all relevant study documents. Team work between different health professionals is considered as a key to deliver high quality primary care [53]. To establish interdisciplinary team working in primary care, communication is a main facilitator [54]. In order to stimulate the interdisciplinary exchange between GPs and PTs, we will perform a workshop after 8 weeks to share experiences and ideas. To improve the patients’ adherence and motivation even in the absence of informal caregivers, we involve home care services which receive a pocket card containing reminders on relevant study topics (e.g. filling physical activity diary). In addition, patients will be assisted by the study team in filling in the questionnaires and the physical activity diary. The physical activity diary and the corresponding manual were revised to make it more understandable and easier to be filled in for the target group. The assessment of physical activity behaviour by the International Physical Activity Questionnaire [55] and the use the actigraphy device StepWatch™ resulted in missing values or seemed not to be appropriate for our target population as reported in other studies [56, 57]; thus, it would not be used in the present study anymore.

The aim of the present study is to evaluate the effectiveness of this complex intervention and to understand the change processes. We expect a behaviour change at cluster and individual level in the intervention group and thus a more effective management of VDB and an improvement in the quality of care, which in turn leads to improvements in the mobility and participation of older community-dwelling adults with VDB.

If the efficacy of the intervention has been proven successful, a refinement of the intervention is planned according to the recommendations of the evaluation study and then strive for transferring it into standard care. To realise this, we are cooperating with a regional statutory health insurance.

## Trial status

Protocol version 1.1, 07.12.2022. The study started in June 2020 and the recruitment of clusters began in October 2021. The first cluster was included in December 2021, and the last cluster will be included in January 2023. Recruitment was stopped between January and March 2022 due to rising incidence of COVID-19 infections and the high burden on GP practices in Germany. Since the length of the recruitment stop was not predictable and a relevant change in study procedures was considered, we decided not to publish the study protocol until the situation became clearer again.

## Data Availability

The GP checklist and decision tree will be made available on reasonable request after the termination of the study. The consent materials are available from the corresponding author on request.

## Abbreviations

COM-B: Capability, opportunity and motivation behaviour
CPW: Care pathway
DHI: Dizziness Handicap Inventory
GP: General practitioner
ICD: International Statistical Classification of Diseases and Related Health Problems
PT: Physiotherapist
SPIRIT: Standard Protocol Items: Recommendations for Interventional Trials
QALY: Quality-adjusted life year
VDB: Vertigo, dizziness or balance disorders
